### Outcomes

#### Primary outcome measure

The primary outcome is the incidence of PEP in the ice water and control groups. PEP is defined as the onset of abdominal pain within 24 h of ERCP and elevation of serum amylase and lipase levels to at least three times the upper limit of normal based on the Cotton criteria[15].

#### Secondary outcome measures

The secondary outcomes are as follows: (1) incidence of PEP in cases of difficult cannulation, (2) incidence of PEP by various ERCP procedures, (3) incidence of PEP by the presence of pancreatic duct cannulation and pancreatography, (4) incidence of PEP by cannulation time, (5) incidence of moderate and severe PEP, (6) incidence of PEP by high-risk factors for PEP, and (7) incidence of other complications.

### Definitions

The severity of PEP is classified as follows, modifying Cotton criteria: mild disease, which requires 2–3 days of fasting; moderate disease, which requires 4–10 days of fasting; and severe disease, which requires 11 or more days of fasting[15]. In addition to the above, patients with necrosis or pseudocyst formation or those who underwent percutaneous drainage or surgery were defined to have severe disease[15].

Difficult cannulation is defined as contact with the papilla more than five times, cannulation time more than 5 min, and unintentional pancreatic duct cannulation more than two times [1]. Definition and severity of cholangitis prior to ERCP; in accordance with Tokyo Guidelines 2018[16]. ERCP trainee is defined as a physician with less than 200 cases of ERCP experience. The following factors have been identified as risk factors for PEP: (1) pre-cut sphincterotomy, (2) endoscopic pancreatic sphincterotomy, (3) endoscopic papillary balloon dilation, (4) difficult cannulation cases, (5) pancreatography, (6) female patients under 60 years old, (7) suspected SOD, (8) history of recurrent pancreatitis, and (9) history of PEP[1].

Regarding other ERCP comorbidities, hemorrhage is defined as hematemesis or a drop in hemoglobin concentration of > 2 g/dL and perforation as the presence of air or intestinal contents beyond the intestinal tract[17]. Other comorbidities and their severity follow the ASGE guidelines[17].

The ice water used in this study is defined as 250 mL of chilled water in a refrigerator with ten ice cubes made with an ice machine.

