## Background

Endoscopic retrograde cholangiopancreatography (ERCP) is indispensable for the diagnosis and treatment of biliopancreatic diseases; post-endoscopic retrograde cholangiopancreatography pancreatitis (PEP) is the most problematic procedure-related adverse event. The incidence of PEP is approximately 3.5–9.7%, with severity and mortality rates of 0.04–0.2% and 0.1–0.7%, respectively [1]. Risk factors for PEP include sphincter of Oddi dysfunction (SOD), female sex, history of pancreatitis, history of PEP, difficulty in bile duct cannulation, insertion of a guidewire into the pancreatic duct, and contrast injection into the pancreatic duct [1]. The main cause of PEP is thought to be papillary edema associated with the procedure. Endoscopic techniques, such as prophylactic pancreatic stenting [2–4], wire-guided cannulation [5, 6], and the use of rotatable catheters [7], have been reported to be effective methods for preventing PEP; however, they are not reliable. Various drugs have been studied to suppress papillary edema, but currently, none has been shown to be useful except nonsteroidal anti-inflammatory drugs (NSAIDs) suppositories [8–10]. Prophylactic administration of NSAIDs suppositories into the rectum prior to ERCP has been reported to significantly reduce the incidence of PEP [11–13] and is now widely used. However, NSAIDs are contraindicated in patients with renal failure, aspirin asthma, gastric ulcers, in the elderly, or in patients with allergies.

For prevention of PEP, we are investigating a new and simple method that can be performed by anyone. Cooling is widely known to be effective in treating acute inflammation and edema in burns. Similarly, we hypothesized that cooling the papilla of Vater would help reduce papillary edema. Our previous single-center prospective study suggested that cooling the papilla with ice water may reduce the incidence of PEP by 4% [14]. However, the results of this trial are uncertain because it is only a single-arm prospective study. This uncertainty has led to a call for randomized controlled trials to validate the results.

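### The three criteria for difficult cannulation are joined by 'and', so read literally all three must be met, which shrinks the subgroup for secondary outcome (1) and risk factor (4)

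*Protocol article*

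**What the plan says.** The Definitions section gives the rule in one sentence: "Difficult cannulation is defined as contact with the papilla more than five times, cannulation time more than 5 min", followed by "and unintentional pancreatic duct cannulation more than two times". It cites reference [1]. The sentence contains no 'or' or 'any of', and nothing elsewhere in the article alters the connective.

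The term is used in two places:

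- Secondary outcome (1) is the "incidence of PEP in cases of difficult cannulation".
- Item (4) of the nine PEP risk factors in Definitions is "difficult cannulation cases". That list underlies secondary outcome (6), PEP by high-risk factors.

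The Allocation section stratifies by whether the procedure is for bile duct cannulation or otherwise, so procedures aimed at the pancreatic duct, or at both ducts, are enrolled. The Interventions section names cannulation time and number of papillary contacts among the items on the findings form. The Statistical analysis section compares the two arms within subgroups, using odds ratios and Fisher's exact test.

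**The concern.** With 'and', failing any one criterion makes a case not difficult. Two kinds of patient are affected.

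- **Prolonged biliary cannulation.** A case far beyond both the contact and the time limits is not difficult if the pancreatic duct was entered unintentionally twice or less.
- **Pancreatic duct as the target.** Intended entry is not unintentional, so the third criterion can hardly ever be met, however hard the cannulation was.

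At stake is who enters the difficult-cannulation subgroup and who carries risk factor (4). A much smaller subgroup gives a much less precise estimate of the ice water effect in it. The wording also leaves room for the eight hospitals to apply the term differently if sites set the flag themselves.

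**Working it through.** **1. The plan's own figure.** The Sample size section uses 10% versus 5%, two-sided α = 0.05 and power 0.8, and states 435 per arm. With the pooled-variance formula and no continuity correction:

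n = [1.96·√(2·0.075·0.925) + 0.8416·√(0.10·0.90 + 0.05·0.95)]² / 0.05² = (0.7301 + 0.3121)² / 0.0025 = 434.4, so 435.

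The figure reproduces. It does not use the definition of difficult cannulation, so it stays the same under either reading. The enrolment target is 440 per arm, 880 in all.

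**2. Logic check.** Take a patient with contacts above the limit, time above the limit and pancreatic entries not above the limit. Under 'all three' the patient is not difficult; under 'any one' the patient is difficult. The label depends on the connective alone.

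**3. Bounds that need no model.** For criteria A, B and C:

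- P(A and B and C) ≤ the smallest of the three prevalences.
- P(A or B or C) ≥ the largest of the three prevalences.

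**4. Illustration on assumed prevalences.** The documents give none, so all of these are assumptions: contacts and time each 30–50%, pancreatic entry 10–20%, and a common latent correlation of 0 to 0.6 in a trivariate normal model. At correlation 0 the arithmetic can be done by hand:

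- 30/30/10%: all three = 0.3·0.3·0.1 = 0.009, or 8 of 880. Any one = 1 − 0.7·0.7·0.9 = 0.559, or 492.
- 50/50/20%: all three = 0.5·0.5·0.2 = 0.05, or 44. Any one = 1 − 0.5·0.5·0.8 = 0.80, or 704.

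| Contacts / time / pancreatic | Correlation | All three (of 880) | Any one (of 880) | Contacts and time met, pancreatic not |
|---|---|---|---|---|
| 30/30/10% | 0 | 8 | 492 | 71 |
| 30/30/10% | 0.3 | 26 | 441 | 87 |
| 30/30/10% | 0.6 | 52 | 386 | 100 |
| 40/40/15% | 0 | 21 | 611 | 120 |
| 40/40/15% | 0.3 | 51 | 550 | 131 |
| 40/40/15% | 0.6 | 88 | 489 | 139 |
| 50/50/20% | 0 | 44 | 704 | 176 |
| 50/50/20% | 0.3 | 84 | 643 | 178 |
| 50/50/20% | 0.6 | 129 | 580 | 181 |

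The smallest ratio in any row is 580/129, about 4.5.

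**5. Precision.** Take the 88-patient row, 44 per arm. With PEP in 4 of 44, the Clopper-Pearson 95% interval for one arm is 2.5–21.7%. With 18 of 176, just below the low end of the 'any one' range (386/2 = 193 per arm), it is 6.2–15.7%.

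Normal-approximation power for 10% versus 5% is Φ[(0.05·√n − 0.7301)/0.3708]:

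- at 64.5 per arm (129/2, the top of the 'all three' range): 19%
- at 193 per arm (386/2): 46%
- at 352 per arm (704/2, the top of the 'any one' range): 71%

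**The case against.** **The intended rule is unknown.** A list joined by 'and' can also enumerate separate signs of difficulty, and reference [1] is not at hand. This stands: the documents do not prove that an all-three rule was meant, or that patients are in fact being misclassified. Against it, the article marks alternatives elsewhere. The exclusion criteria apply if any single one is met, and the extra conditions for severe disease are joined by 'or'. The literal reading is therefore the natural one, and if alternatives were meant the wording is wrong.

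**The Background does not settle it.** It lists "difficulty in bile duct cannulation, insertion of a guidewire into the pancreatic duct" as separate items, and a reader might infer that 'and' wrongly merges them. An 'any of' rule would merge them too, since repeated pancreatic entry alone would then count as difficulty. The argument does not discriminate between the readings.

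**No dilution of a reference group.** A reader might infer that difficult cases left among the non-difficult dilute the result. The planned comparison is ice water against control within subgroups, so a stricter rule makes the subgroup smaller and more selected; it does not dilute the treatment comparison inside it.

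**The loss is partly covered.** Secondary outcome (4) still analyses PEP by cannulation time. If high risk means any of the nine factors, some patients missed by item (4) would qualify through another. Even the larger subgroup falls short of 80% power for 10% versus 5% in the illustration. These points limit the harm but leave secondary outcome (1) resting on the rule as worded.

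**Conclusion.** The point holds as a fault in a stated rule for secondary analyses. Taken literally, the definition excludes prolonged, many-contact cannulations without repeated unintended pancreatic entry, and almost all procedures aimed at the pancreatic duct. Under the assumptions above, the subgroup is about 1–15% of patients (8–129 of 880) instead of about 44–80% (386–704). The model-free bounds fix the direction; the sizes rest entirely on assumed prevalences and correlations.

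The reach is limited. The protocol lists seven secondary outcomes and ranks none of them as key, so that weight should not be read into it. The primary outcome, its test and the 435 per arm are untouched. Nor does the definition bias the randomized comparison: it is the same in both arms, and difficulty arises before the ice water is given at the end of the procedure.

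**What to change.** Before analysis:

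1. Check the definition against reference [1] and reword it as 'one or more of' the three criteria. If all three are truly required, say so explicitly.
2. State how the third criterion applies when the pancreatic duct is the intended target.
3. Confirm that the number of unintended pancreatic duct entries is recorded. The Interventions text names time and contacts but not this count; the findings form, which is not shown, may include it.
4. Derive the flag centrally from the recorded components, with no separate site judgement.

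The cost is a wording change and one derived variable. If the third count is not yet captured, it also needs one added field. The sample size and primary analysis do not change. Settling the connective before outcomes are seen also prevents subgroup membership from being chosen afterwards.

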**Methods:**

This study is being conducted at eight hospitals in Japan starting in April 2022. Patients undergoing ERCP will be randomized to ice water group and control group. In the ice water group, 250 ml of ice water is injected toward the papilla at the end of ERCP. The next morning, a physical examination and blood tests are performed to evaluate for the development of pancreatitis. The goal is to have 440 cases in each group.

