**Fig. 2 Fig2:**
[figure not shown]
Study protocol. ^※^Baseline variables: age, sex, ECOG-PS, ASA-PS, history of acute or recurrent pancreatitis, serum total bilirubin level before ERCP, serum amylase level before ERCP, ERCP indication, and presence of SOD, cholangitis, pancreatic duct obstruction at the head of the pancreas. ^Primary outcome: presence of PEP. ^#^Secondary outcomes: presence of PEP in cases of difficult cannulation, PEP by various ERCP procedures, PEP by the presence of pancreatic duct cannulation and pancreatography, PEP by cannulation time, moderate and severe PEP, and PEP by high-risk factors for PEP

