**Fig. 3 Fig3:**
[figure not shown]
Findings form

The patient’s symptoms are monitored after ERCP. The next morning, medical examination is performed to determine if the patient meets the criteria for PEP, and if the patient experiences abdominal pain, blood tests may be performed at the discretion of the physician in charge.

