### Sample size

#### Number of patients

Without any form of prophylaxis, the incidence of PEP in the native papilla can reach 10–15% as reported in previous studies[1, 11, 18, 19]. Our previous study revealed that ice water injection reduced the incidence of PEP from 11 to 4%, and the relative risk reduction was 63.6%[14]. Assuming a baseline PEP risk of 10% in normal native papilla, a two-sided α = 0.05 and a power of 0.8, 435 patients per study arm are required to detect a 50% reduction in the incidence of PEP to 5%. This absolute reduction in incidence is believed to be clinically relevant and substantial enough to change the existing clinical practice. We aim to enroll 440 patients into each group to accommodate patients who will be lost to follow-up, missing data, or withdrawal of consent.

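### The haemorrhage definition leaves out melaena, and the article does not secure the haemoglobin route, so some papillary bleeds could be recorded as no haemorrhage

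*Protocol article*

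**What the plan says.** Haemorrhage enters the trial through the last item under Secondary outcome measures, "7) incidence of other complications", and through the secondary objective, which covers other adverse events. The Definitions section gives the rule: "hemorrhage is defined as hematemesis or a drop in hemoglobin concentration of > 2 g/dL". Perforation is defined in the same sentence. The next sentence adds "Other comorbidities and their severity follow the ASGE guidelines", which by its wording concerns complications other than those just defined.

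On how a haemoglobin fall would come to light:

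- The Abstract (Methods) says "The next morning, a physical examination and blood tests are performed to evaluate for the development of pancreatitis".
- The Interventions section (text under Fig. 3) says "The patient’s symptoms are monitored after ERCP" and then, of the next-morning examination, "if the patient experiences abdominal pain, blood tests may be performed at the discretion of the physician in charge".
- The Fig. 2 caption lists among the baseline variables "serum total bilirubin level before ERCP, serum amylase level before ERCP". Haemoglobin is not in that list.

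**The concern.** The definition is closed, with two ways in: vomited blood, or a measured fall in haemoglobin. All participants have a native papilla, and the procedures that the article lists as risk factors include pre-cut sphincterotomy, pancreatic sphincterotomy and balloon dilation. A bleed at that site can drain onward into the bowel. A patient with documented melaena and no haematemesis is then scored as having no haemorrhage unless someone has measured haemoglobin and found a sufficient fall.

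Haemorrhage is one of only two complications for which the article writes its own definition, and the article describes the method as safe. A trial that is to support that description should count an overt bleed as a bleed.

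**Working it through.** **1. The plan's own figure.** The only design figure is the sample size for the primary outcome: "a two-sided α = 0.05 and a power of 0.8, 435 patients per study arm are required", for 10% against 5%. With pooled variance and no continuity correction,

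n = [1.960·√(2·0.075·0.925) + 0.842·√(0.10·0.90 + 0.05·0.95)]² / 0.05² = (0.730 + 0.312)² / 0.0025 ≈ 434.4, rounded up to 435.

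The figure reproduces. It does not involve haemorrhage, so nothing below alters it.

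**2. The definition applied to possible cases.**

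| Presentation | Haemoglobin fall > 2 g/dL documented | Recorded as haemorrhage |
|---|---|---|
| Haematemesis | yes or no | yes |
| Melaena only | yes | yes |
| Melaena only | measured, smaller fall | no |
| Melaena only | not measured, or no earlier value | no |

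The last two rows are the gap. The guideline sentence does not clearly close it, because it refers to other complications and haemorrhage has already been defined.

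**3. Is the haemoglobin route secured?** Setting the two statements side by side:

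- Abstract: next-morning blood tests, without condition, for the purpose of detecting pancreatitis.
- Interventions: blood tests only where there is abdominal pain, and then optional.

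These conflict. Haemoglobin is named in neither. Under the Interventions wording, a patient without pain need have no next-morning sample. The definition also does not say from which value the drop is measured.

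**4. Size.** The article gives no bleeding rate, no share of bleeds showing only as melaena, and no share with haemoglobin results. The number missed therefore cannot be derived. The table below is an illustration under two assumptions: a true bleeding rate r, and a share c of bleeds captured, equal in both arms. Expected recorded bleeds per arm are 440·r·c. Power is for a doubling of the recorded rate (r·c against 2·r·c), 440 per arm, two-sided 5%, normal approximation.

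| Assumed r | c = 100% | c = 75% | c = 50% | c = 25% |
|---|---|---|---|---|
| 1% | 4.4 bleeds; 0.230 | 3.3; 0.183 | 2.2; 0.135 | 1.1; 0.088 |
| 2% | 8.8; 0.412 | 6.6; 0.323 | 4.4; 0.230 | 2.2; 0.135 |
| 5% | 22.0; 0.805 | 16.5; 0.676 | 11.0; 0.497 | 5.5; 0.276 |

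With equal capture, the ratio between arms is preserved (2rc/rc = 2r/r), while absolute rates are understated by the factor c and precision falls. The table shows direction only; neither r nor c comes from the article.

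**The case against.** The strongest reply has four parts.

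- **The article is a condensation.** Laboratory schedules and case report form fields normally sit in the full protocol. The Fig. 2 caption is a list of baseline variables, not a laboratory schedule, and the findings form is not shown. This stands: the article's silence does not show that haemoglobin goes unmeasured. A reader might infer that it is not routinely measured, but the Abstract's unconditional statement on blood tests speaks against that. What can be checked is the conflict between the two statements.
- **The pain-triggered blood test concerns the check for pancreatitis.** It does not forbid tests for suspected bleeding, and symptoms are monitored. This also stands. A melaena case with a sufficient measured fall counts under the present wording. But nothing in the definition makes that measurement happen, and an overt bleed with a smaller fall is excluded even when it is measured.
- **The definition is referenced to a guideline.** That source is not at hand, so no departure from it is alleged. The point rests on what the stated rule does in a trial of the duodenal papilla.
- **The impact is small.** At assumed rates of 1–2%, even full capture leaves power of only 0.23–0.41 to detect a doubling. This stands as a limit on the point's weight, but with so few events each omitted one matters more to the description of safety.

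A reader might also infer a bias in favour of ice water: only the patient is stated to be blinded, and if testing follows pain, fewer ice-water patients might be tested. At the planned rates, 440 × 10% = 44 control and 440 × 5% = 22 ice-water patients would have pancreatitis, and hence pain. Unequal testing is possible, but the article does not show it: the same definition applies to both arms, pain has other causes, and the blood-test statements conflict.

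**Conclusion.** The point holds in a limited form. The stated definition does not count melaena, so some papillary bleeds without haematemesis would be recorded as no haemorrhage unless a haemoglobin fall above 2 g/dL happened to be documented, and the article does not secure that documentation.

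It would be tempting to say that most papillary bleeding goes unrecorded. No figure in the article supports that, and the share missed cannot be computed.

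The consequence is confined to one component of a secondary safety outcome: understated bleeding rates and less precision, with a possible but undemonstrated difference in ascertainment between arms. The primary outcome definition and the 435 per arm are untouched. The conclusion assumes only that a bleed at the papilla can pass downstream without being vomited. It is worth correcting because the correction is cheap.

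**What to change.** 1. For secondary outcome (7), define haemorrhage as haematemesis and/or melaena, or a haemoglobin fall above 2 g/dL from the pre-ERCP value. Apply it identically in both arms from the medical records, which the Data collection section already names as source data. Enrolment was ongoing, so melaena documented for patients already included can be captured too.
2. Reconcile the Abstract and the Interventions text on whether next-day blood tests are done in all patients or only in some.
3. Record haemoglobin, before and after ERCP, wherever blood is already drawn. This adds no sampling; requiring a next-morning value in every patient could add a blood draw and is not needed for this correction.

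**Cost:** a change of wording, a few case report form fields, and a look back through the records of patients already enrolled. A few minor melaena episodes will be counted as haemorrhage. Where no paired haemoglobin exists, a silent fall will still be missed. The sample size and primary analysis do not change.

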### Sample size

#### Number of patients

Without any form of prophylaxis, the incidence of PEP in the native papilla can reach 10–15% as reported in previous studies[1, 11, 18, 19]. Our previous study revealed that ice water injection reduced the incidence of PEP from 11 to 4%, and the relative risk reduction was 63.6%[14]. Assuming a baseline PEP risk of 10% in normal native papilla, a two-sided α = 0.05 and a power of 0.8, 435 patients per study arm are required to detect a 50% reduction in the incidence of PEP to 5%. This absolute reduction in incidence is believed to be clinically relevant and substantial enough to change the existing clinical practice. We aim to enroll 440 patients into each group to accommodate patients who will be lost to follow-up, missing data, or withdrawal of consent.

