### Assigning interventions

#### Allocation

Randomization is centralized, web-based, and accessible 24 h a day; it is balanced (1:1) and stratified by center and the cause of the indication for ERCP [for bile duct cannulation or otherwise (for pancreatic duct and both bile and pancreatic ducts cannulation)].

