#### Statistical analysis

The full analysis set (FAS) is the population of patients enrolled in the study, excluding duplicate or erroneous enrollments, cases of inadequate study treatment, and cases in which no post-assignment data are available.

The per-protocol set (PPS) excludes FAS cases in which efficacy could not be assessed due to inadequate observation, etc., and cases of serious deviation from or violation of the study protocol.

For each allocation group, the percentage of PEP occurrences will be calculated using the number of FAS cases as the denominator. The exact 95% confidence intervals (CI) of Clopper and Pearson will be calculated. The frequencies, expression proportions, and 95% CI will also be calculated for each group. Fisher's exact test will be used to compare the groups. The test will be two-tailed with a significance level of 5%. The same analysis will be performed for PPS as a reference.

After dividing the patients into subgroups according to background factors, comparisons between the groups will be made. Binary data (PEP and other comorbidities) will be evaluated using odds ratios and 95% CI, and compared using Fisher's exact test. When the background factor is a continuous variable, subgroups will be created based on the median value. The results of the subgroup analysis will be graphically represented by a forest plot.

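### The 435 per arm fits an uncorrected chi-square test, but the plan tests with Fisher's exact test, whose power at 440 per arm is about 78%, not 80%

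*Protocol article*

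**What the plan says.** Protocol article, Sample size (Number of patients). The design assumptions are "Assuming a baseline PEP risk of 10% in normal native papilla" and "a two-sided α = 0.05 and a power of 0.8". From these the article concludes that "435 patients per study arm are required to detect a 50% reduction in the incidence of PEP to 5" per cent. It does not name the test or formula behind the 435. It then adds a margin: "We aim to enroll 440 patients into each group to accommodate patients who will be lost to follow-up, missing data, or withdrawal of consent". No expected loss rate is given.

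Protocol article, Statistical analysis. For the primary outcome, the PEP proportion in the full analysis set, "Fisher's exact test will be used to compare the groups". "The test will be two-tailed with a significance level of 5" per cent.

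Protocol article, Allocation. Randomization is 1:1, so the two arms have equal planned size.

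**The concern.** A stated power holds only for a particular test. Fisher's exact test conditions on the total number of events and, with discrete counts, rejects less often than its nominal level allows. At a given sample size it therefore has less power than the uncorrected chi-square test. If 435 was computed for the chi-square test, the 80% does not describe the analysis that the same article prescribes.

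The second part is the margin. Five extra patients per arm are meant to absorb three kinds of loss, and the article does not say how much loss was expected. If the base figure is already short for Fisher's test, the margin cannot be read as protecting 80%.

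At stake is the chance of missing a real halving of PEP, and the accuracy of the figure that justifies enrolling 880 patients.

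**Working it through.** **Inputs.** Control rate 10%, ice water rate 5%, two-sided α 0.05, power 0.80, 435 required and 440 enrolled per arm (Number of patients); 1:1 allocation (Allocation); two-tailed Fisher's exact test at 5% (Statistical analysis).

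**Step 1: reproduce the 435.** The pooled-variance formula without continuity correction is

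n = [z₀.₉₇₅·√(2p̄(1−p̄)) + z₀.₈·√(p₁(1−p₁) + p₂(1−p₂))]² / (p₁−p₂)²

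with p̄ = 0.075:

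- √(2 × 0.075 × 0.925) = √0.13875 = 0.3725, times 1.960 = 0.7301
- √(0.09 + 0.0475) = √0.1375 = 0.3708, times 0.8416 = 0.3121
- n = (0.7301 + 0.3121)² / 0.0025 = 434.4, so 435.

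Other two-sided formulas give different numbers:

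| Formula | n per arm |
|---|---|
| Pooled, uncorrected | 435 |
| Unpooled variance | 432 |
| Arcsine | 424 |
| Continuity-corrected (approximates Fisher's test) | 474 |

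The stated 435 is therefore reproduced exactly, and only by the uncorrected pooled formula.

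**Step 2: power under the planned test.** Power is the sum, over all pairs of event counts, of Bin(x₁; n, 0.10) × Bin(x₂; n, 0.05) for the pairs where the two-sided Fisher p-value is at most 0.05. The p-value sums the tables no more probable than the one observed; doubling the one-sided p-value gives the same power. The uncorrected chi-square test is enumerated in the same way.

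| Evaluable per arm | Fisher | Uncorrected chi-square |
|---|---|---|
| 435 | 77.1% | 81.1% |
| 440 | 77.7% | 81.6% |
| 465 | 79.995% | 83.4% |
| 466 | 80.1% | 83.5% |

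Against the stated 80%, the gap is 2.9 points at 435 and 2.3 points at 440. Fisher's test first reaches 80% at 466 per arm, which is 466 − 435 = 31 more than stated.

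**Step 3: actual size of the tests at 440 per arm.** For common rates from 5% to 10%, Fisher's two-sided type I error is 3.5% to 3.8%. The uncorrected chi-square test runs at 4.9% to 5.1%.

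**Step 4: the margin.** (440 − 435)/440 = 5/440 = 1.1%. No loss rate is stated, so the rates below are assumptions for illustration, applied to 440 per arm.

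| Assumed loss | Evaluable per arm | Fisher | Uncorrected chi-square |
|---|---|---|---|
| 2% | 431 | 76.6% | 80.7% |
| 5% | 418 | 75.4% | 79.5% |
| 10% | 396 | 73.2% | 77.1% |

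Under Fisher's test the type II error is thus 22.3% with no losses and 26.8% at 10% loss, against the planned 20%.

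**The case against.** Five points can be made for the plan.

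- *The gap is small and a positive result is safe.* This stands. Fisher's test runs below its nominal level, so the mismatch costs power and nothing else. A reader might infer that the primary comparison is invalid or biased; nothing in the article supports that.
- *The assumed rates are cautious.* The article cites 10% to 15% for unprotected native papilla and a previous result of 11% against 4%. At 12% against 6%, Fisher's power is 85.9% with 440 per arm and 81.9% with 396; at 11% against 4% it is 97.5% with 440. So a 2 to 3 point gap is small beside the uncertainty in the rates. But this does not make the stated 80% true at the stated 10% against 5%.
- *Losses may be very low.* PEP is defined by onset within 24 hours and patients are examined the next morning. A reader might infer that 1.1% is too small, or that any realistic loss pushes power well down. The article gives no loss rate, so it does not show this; only the arithmetic of the margin and a conditional range can be stated. Against complacency, the full analysis set also drops patients with inadequate study treatment, which is not among the losses the margin is said to cover.
- *The basis of the 435 is inferred.* True, but the conclusion does not depend on it: Fisher's power at 435 is 77.1% whichever formula was used.
- *A stratified test would suit the stratified randomization.* One might infer that a Cochran-Mantel-Haenszel test restores the power. No calculation supports this: the 81.6% belongs to the unstratified chi-square test, and the strata could number up to 16 (eight centers by two indication groups).

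**Conclusion.** The point holds at moderate severity. The sample size section and the analysis section do not fit together: the stated rates, α, power and 435 per arm agree for the uncorrected chi-square test, but not for the Fisher's exact test that the article prescribes. At 10% against 5%, Fisher's power is 77.7% with all 440 per arm evaluable and 77.1% with 435; about 466 per arm are needed for 80%. The margin to 440 corresponds to 1.1% attrition.

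The Fisher figures rest on the article's own rates, equal arms and independent binomial outcomes. The figures with losses (76.6% to 73.2%) rest also on assumed loss rates of 2% to 10%. The error is in the stated power. It introduces no bias and does not inflate the type I error.

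**What to change.** **Main change.** In Number of patients, name the test and restate the power for the planned two-tailed Fisher's exact test: about 78% for 10% against 5% with 440 evaluable per arm, and about 73% to 77% for losses of 10% to 2%. State that, relative to 435, the 440 allows for 1.1% attrition. This changes wording only and needs no more patients; the cost is a slightly less favorable stated power.

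**Option.** Make the unstratified, uncorrected chi-square test primary and keep Fisher's test as a sensitivity analysis. Power is then about 82% at 440 per arm and 79.5% at 5% loss, so losses of that order would still leave it marginally under 80%. This is more than wording: enrollment is under way, so it amends the primary analysis of a running trial and must be fixed before anyone sees outcomes by arm. It also gives up Fisher's guarantee on the 5% level for an exact size of 4.9% to 5.1% at common rates of 5% to 10%.
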